### Methods in analysis to handle protocol non-adherence and any statistical methods to handle missing data {20c}

For time to event endpoints, we will censor the patient at the date of last follow-up unless the patient is documented to have an event. We will attempt to contact the patients telephonically or by other methods to ensure adherence to follow up. If more than 10% of the patients have missing data, then an additional sensitivity analysis will be undertaken where all lost to follow up patients would be assumed to have the event of interest. For quality of life data, we will under complete case analysis and as a sensitivity analysis missing values will be imputed using an imputation based approach.

Finally, as this is a non-inferiority trial, if there is high non-compliance with the test treatment, then an analysis of only those receiving per-protocol treatment will be conducted separately.

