#### Sample size

The sample is calculated based on the assumption that the 5-year local recurrence rate in the control arm is 5% with an exponential distribution. We hypothesize that the use of 1-week course of adjuvant radiotherapy will not increase the locoregional recurrence beyond 8% (absolute difference of 3%), corresponding to a hazard ratio of 1.63. We further assume that patients will be accrued over 5 years with an initial ramp-up in the first year and that 2% of the patients will be lost to follow-up each year of the trial. The total trial duration is expected to be 10 years to ensure a minimum follow-up of 5 years for the last patient. For a fixed sample size design to achieve the required number of events to achieve a one-sided type I error of 0.025 and a power of 80% the total number of events required is 140. The total planned sample size is 2100 patients.

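### Counting every lost patient in both arms as a recurrence dilutes the hazard ratio when loss is similar between arms, so the sensitivity analysis is easier to pass than the primary analysis

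*Protocol article*

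**What the plan says.** In section 20c (protocol non-adherence and missing data), time-to-event endpoints are censored at last follow-up in the main analysis. If more than 10% of patients have missing data, one further analysis is run "where all lost to follow up patients would be assumed to have the event of interest". No arm is named, and the date at which the assumed event is placed is not given. The article shows no other missing-data analysis for these endpoints.

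Three other parts of the article bear on this:

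- **Criterion.** Section 20a judges non-inferiority on the upper 95% limit of the Cox hazard ratio against 1.63. I read this as requiring the limit to lie below 1.63, as Table 4 implies, although that sentence is worded the other way round.
- **Loss.** The Sample size section assumes that "2% of the patients will be lost to follow-up each year of the trial", without a difference by arm. The Discussion adds that keeping patients in long follow-up is a real difficulty in this population.
- **Follow-up.** The Sample size section states: "The total trial duration is expected to be 10 years to ensure a minimum follow-up of 5 years for the last patient". The visit schedule in Table 3 ends at 60 months after radiotherapy, and the primary objective concerns recurrence by 5 years.

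**The concern.** Treating all lost patients as failures is often thought of as a worst case. In a ratio-based non-inferiority comparison it is not one. When loss is similar in the two arms, the same artificial hazard is added to both, which shrinks any true relative excess in the test arm. The extra events also narrow the confidence interval. Both effects make the limit of 1.63 easier to meet, and higher loss strengthens them.

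A check that becomes easier to pass as data quality falls is not a robustness check. If the censored analysis met the limit and this one agreed, readers would take the agreement as evidence that loss to follow-up did not matter, when it would carry little information on that question.

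**Working it through.** **Inputs (Sample size section unless stated).** "5-year local recurrence rate in the control arm is 5% with an exponential distribution"; margin of 8% against 5%, hazard ratio 1.63; 2% annual loss; "patients will be accrued over 5 years with an initial ramp-up in the first year"; 10 years in total; 2100 patients; 1:1 allocation (section 16a).

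**Assumptions.** Loss is equal in both arms and independent of recurrence; the first-year accrual rate is half the later rate; an assumed event falls at the date of loss; deaths are not modelled.

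**The plan's own figures first.**
- Margin: ln 0.92 / ln 0.95 = 1.626, as stated.
- Events, by Freedman's formula: (2.63/0.63)² × (1.96 + 0.84)² ≈ 137, against the stated 140. Schoenfeld's formula gives 132.
- With the accrual assumption above, 2100 patients give about 140 events at a true hazard ratio of 1.
- Hazard ratio at the final bound: 1.63 × exp(−1.96 × 2/√140) = 1.17, as in Table 4.

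**Step 1: annual hazards.**
- Control recurrence: −ln(0.95)/5 = 0.01026.
- Test recurrence at the margin: 1.63 × 0.01026 = 0.01672.
- Loss: −ln(0.98) = 0.02020.

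**Step 2: how many are lost.** For recurrence hazard h, loss hazard e and follow-up f, the fraction lost before an event is e/(h+e) × (1 − exp(−f(h+e))).
- Follow-up to calendar year 10: mean accrual time is (0.5/4.5) × 0.5 + (4/4.5) × 3 = 2.72 years, so mean f is 7.28. The fraction is 13.2% in control and 12.9% in test at hazard ratio 1.63, or about 275 patients. Varying the first-year rate from 25% to 100% of the later rate keeps it between 12.8% and 13.5%.
- Follow-up stopped at 5 years: 9.4% and 9.2%, about 9.3% overall, just under the 10% trigger.

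**Step 3: what the rule estimates.** If loss counts as an event, each arm's hazard is recurrence plus loss.
- True 1.63: (0.0167 + 0.0202)/(0.0103 + 0.0202) = 1.21.
- True 2.0: (0.0205 + 0.0202)/(0.0103 + 0.0202) = 1.34.

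**Step 4: chance of meeting the limit, in closed form.**
- True 1.63: about 181 real plus 273 imputed events, 454 in all. The standard error is 2/√454 = 0.094; ln(1.63/1.212)/0.094 = 3.16; 3.16 − 1.96 = 1.20; probability about 88%.
- True 2.0: 205 + 271 = 476 events. The standard error is 0.092; ln(1.63/1.337)/0.092 = 2.16; 2.16 − 1.96 = 0.20; probability about 58%.

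**Step 5: simulation (2000 trials per row, Cox model, follow-up to year 10).**

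| True HR | Annual loss, each arm | Primary: limit met | All lost = event: mean HR | All lost = event: limit met |
|---|---|---|---|---|
| 1.00 | 2% | 82% | 1.00 | 99.9% |
| 1.63 | 2% | 2.6% | 1.21 | 88.7% |
| 2.00 | 2% | 0.0% | 1.34 | 57.2% |
| 1.63 | 3% | 2.5% | 1.16 | 97.8% |

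**Step 6: unequal loss (assumed rates, test against control, true hazard ratio 1.63).**
- 2.5% against 1.5%: analysed ratio 1.65, limit met in 1.8%.
- 3% against 1%: ratio 2.31, never met.
- 1.5% against 2.5%: ratio 0.90, always met.

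The result follows relative retention more than recurrence.

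**Step 7: absolute scale.** Under the rule at true 1.63, 5-year failure is 1 − exp(−5 × 0.03046) = 14.1% in control and 1 − exp(−5 × 0.03693) = 16.9% in test, a difference of 2.7 points. The standard error is √[(0.141 × 0.859 + 0.169 × 0.831)/1050] = 1.58 points. The upper limit falls below 3 points with probability Φ((3.0 − 2.73)/1.58 − 1.96) ≈ 4%; simulations gave 3.3% and 4.1%. At true hazard ratio 1 the pass rate falls from 87% for the censored analysis to about half.

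**The case against.** The strongest reply has four parts.

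- **Nothing is decided on this analysis.** It is additional and conditional, and no decision rule is attached to it. This stands. A reader might infer that the trial would declare an inferior schedule non-inferior. The article does not support that: the primary analysis censors lost patients and keeps its one-sided error of about 2.5%.
- **The direction depends on loss by arm.** This also stands. A reader might infer that the rule always drives the hazard ratio to 1. It moves it towards the ratio of the loss rates, only part of the way (1.63 to 1.21 at equal loss), and clearly higher loss in the test arm pushes it up. The article gives a single loss rate and no arm difference, so equal loss is the natural planning case, but it is an assumption.
- **The trigger may not be met.** With the 10-year duration it is expected to be. If follow-up ends with the 60-month visit schedule, expected loss is about 9.3%, and the trigger was met in about 13% of simulated trials. The article supports either reading, and its trigger refers to missing data in general.
- **On the absolute 3% margin the rule is a genuine stress test.** Step 7 confirms this. But section 20a fixes the hazard ratio limit as the formal criterion, and section 20c does not move the sensitivity analysis to the other scale.

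These points limit the size of the problem. They do not make the rule suitable for the hazard ratio criterion.

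**Conclusion.** The concern holds in a limited form, and the rule should be fixed. On the trial's formal criterion, with similar loss in both arms at 2% a year and follow-up to year 10, the analysis reports a true hazard ratio of 1.63 as about 1.21. It meets the limit in about 88% of trials, against about 3% for the primary analysis, and in about 57% at a true ratio of 2.0. The consequence is false reassurance about robustness; the primary conclusion is unaffected.

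The size rests on equal, non-informative loss, events placed at the date of loss, and reading the result by hazard ratio. If follow-up stops at 5 years, the analysis would usually not be triggered; the rule itself would still meet the limit in about 75% of trials at a true ratio of 1.63.

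**What to change.** Replace the rule in section 20c, and in the statistical analysis plan if it is repeated there, with a delta-adjusted tipping-point analysis:

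- Impute recurrence after loss at the observed hazard in the control arm and at k times the observed hazard in the test arm, for example k = 1, 1.63, 2 and 3.
- Report the k at which the upper 95% limit of the hazard ratio reaches 1.63.
- Show the 5-year absolute difference alongside.

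Counting only test-arm losses as events is a poor substitute: in simulation it never met the limit, even at a true hazard ratio of 1, so it cannot inform.

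Two independent sets of runs (single imputation with known hazards, so approximate) show that the replacement discriminates:

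| k | Limit met at true HR 1.63 | Limit met at true HR 1 |
|---|---|---|
| 1 | 3.0–3.9% | 83–85% |
| 1.63 (one set only) | 2.2% | 77% |
| 2 | 0.3–1.1% | 72–74% |

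The cost is wording and a little programming, plus a sensitivity analysis that is harder to pass. Sample size, conduct and patient care do not change. It is best settled before outcome data are analysed, because in an open-label trial a later change could look data-driven.

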### Plans to give access to the full protocol, participant level-data and statistical code {31c}

The full protocol as well as the statistical analysis plan is available as supplementary material with the manuscript. At present, there are no plans to make patient-level data available publically, but we will consider the same once primary reporting of the outcomes is completed or as mandated by regulations.

## Oversight and monitoring

### Composition of the coordinating centre and trial steering committee {5d}

The trial will be managed through the CTU at the Tata Medical Center. All PIs of the collaborating institutes will be a part of the trial management committee. Study coordination, monitoring, data acquisition and management and statistical analysis will be performed by Tata Medical Center.

Additionally, we will constitute an outcome assessment committee who will provide an independent and central assessment of the important trial outcomes.

### Composition of the data monitoring committee, its role and reporting structure {21a}

An independent data safety and monitoring committee will be constituted which will provide an independent assessment of the patient safety, trial progress, making recommendations to the trial management committee about the continuation of the trial based on the data made available by the trial investigators. The DSMC will also recommend any revisions in protocol required as a result of new or emerging information regarding the adjuvant radiotherapy schedule for this setting. DSMC reports will be communicated to the institutional review boards of the participating centres. The DSMC will be composed of four to five members of whom at least one will be a statistician with significant experience in clinical trials.

### Adverse event reporting and harms {22}

All adverse events related to radiotherapy as well as any serious adverse events will be recorded in clinical trial forms which will be recorded in the centrally managed RedCap database. The investigator at each site will be responsible for reporting the SAE to the respective Institutional Review Board as well as the PI at the CTU. Local IRB would be notified of any SAE within 24 h on a working day or as per the institutional norm. The sponsor will be intimated within a period of 10 days from the date of occurrence of the SAE. SAEs must be reported up to 30 days from the end of the study intervention.

The following information should be provided for all SAEs:
Event description including classification according to NCI CTCAEPrimary and secondary diagnosis of the event (if death/hospitalization)Severity/worst gradeAttribution to study interventionExpectedness (listed in IB/product information)Action taken with the study interventionImpact of SAE (e.g. hospitalization details)The outcome of SAE including end date if recovered

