### Strategies to improve adhere to intervention {11c}

Patients will be counselled about the need to adhere to the treatment schedule. They will be reviewed weekly during treatment to discuss and manage any treatment-related adverse events they may be encountering. Any missed fraction would be informed to the treating team and attempts will be made to communicate with the patient to avoid this in future.

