#### Secondary outcomes

Overall survival: This is defined as the interval of time between the date of randomization to the date of death due to any cause. We will attempt to obtain the reason for death wherever feasible. The duration will be calculated using the actuarial method and patients who are alive at last follow up will be censored on the same date. Cumulative proportion of patients surviving at 5 years will be reported along with hazard ratio for the two arms.Invasive disease-free survival: This is defined as the time from randomization to the time any recurrence (pre-invasive / invasive), distant metastases, death from any cause and second invasive primaries, including invasive neoplasms of the breast. Cumulative proportion of patients without invasive disease recurrence at 5 years will be reported along with hazard ratio for the two arms.Adverse events (AE): The National Cancer Institute (NCI) Common Terminology Criteria for Adverse Events (CTCAE) version 5 will be used to classify and grade the severity of adverse events. Clinician reported AE grades would be collected in addition to patient-reported outcomes measures to be collected as a part of the assessment of quality of life. Adverse events due to radiotherapy (CTCAE 5.0) will be classified into the following categories:
Start of RT to 90 days after RT: Acute toxicity> 90 days after RT: Late toxicity.Quality of life: Quality of life will be assessed using self-administered EORTC QLQ C30 and the FACT-B questionnaires before the start of radiotherapy, at the end of radiotherapy and then at 6, 12 and 18 months. While various QoL endpoints are of interest, the primary QoL endpoint of interest will be the summary score of EORTC QLQ C30 derived from 15 questions as defined by Giesinger et al. [27]. We will be comparing the proportion of patients in whom the summary score of the EORTC QLQ C30 is equal to or better than the baseline at 12 months in the two arms.

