### Participant timeline {13}

The participant timeline for treatment and assessments is shown in the table below (Table 3).

**Table 3 Tab3:** Participant timeline

Assessment	All follow-up time points are taken from the date of completion of RT					
	Baseline	Adjuvant RT			3–12 months every 3 months after RT	13–60 months every 6 months after RT
		Week 1	Week 2	Week 3		
Clinical evaluation	X					
Eligibility checklist	X					
Informed consent	X					
Randomization	X					
RT QA	Prior to centre initiation and throughout the trial recruitment period					
RT treatment (control arm)		X	X	X		
RT treatment (test arm)		X				
RT verification (Control Arm)		X	X	X		
RT verification (test arm)		X				
SAE		X	X	X	X	X
Acute toxicity		X	X	X		
FU assessments				X	X	X
EORTC QLQ C30 (control arm)	X			X	At 6, 12 and 18 months after completion of RT	
FACT-B (control arm)	X			X	At 6, 12 and 18 months after completion of RT	
EORTC QLQ C30 (experimental arm)	X	X			At 6, 12 and 18 months after completion of RT	
FACT-B (experimental arm)	X	X			At 6, 12 and 18 months after completion of RT	

Note that patients who undergo sequential tumour bed boost will have their post-radiotherapy assessment postponed till boost is completed. This would mean at the 2nd week in patients receiving 1-week RT and the 4th week in patients undergoing 3-week RT

In each study visit, a clinical assessment including a history and examination will be undertaken. Adverse events related to radiotherapy will be recorded in a case record form. Quality of life questionnaires will be administered on the visits as indicated. During the follow-up period patients will undergo mammogram of intact breast(s) at 12–18-month intervals or as per the institutional policy.

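### Acute toxicity is defined to 90 days after radiotherapy but Table 3 schedules it only in weeks 1–3, which covers the two arms unequally after treatment; the 30-day SAE sentence also conflicts with SAE marks to month 60

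*Protocol article*

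**What the plan says.** **Acute toxicity.** Secondary outcomes splits radiotherapy adverse events by timing: "Start of RT to 90 days after RT: Acute toxicity> 90 days after RT: Late toxicity". In Table 3 (Participant timeline {13}) the acute toxicity row is marked in weeks 1, 2 and 3 and is blank in both follow-up columns. That row is not split by arm, although the rows for treatment, verification and questionnaires are. The table header states that "All follow-up time points are taken from the date of completion of RT", and the first follow-up column is "3–12 months every 3 months after RT". The text under the table adds that each study visit includes a history and examination, and that radiotherapy-related adverse events go on a case record form.

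Two analyses draw on these data. Statistical methods {20a} compares the proportion with grade 3–4 adverse events between arms. Interim analyses {21b} examines acute toxicity at 50 patients per arm, with power stated for grade 3 or higher skin toxicity.

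**Serious adverse events.** Adverse event reporting and harms {22} opens with "All adverse events related to radiotherapy as well as any serious adverse events will be recorded in clinical trial forms", with no time limit. It then gives notification times to the local review board (24 hours) and the sponsor (10 days), and ends that paragraph with "SAEs must be reported up to 30 days from the end of the study intervention". Table 3 marks SAEs in weeks 1–3 and in both follow-up columns, the last being "13–60 months every 6 months after RT".

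**The concern.** The acute endpoint has a window that its own assessment schedule does not fill. The marked weeks are counted from the start of treatment. They are therefore all on-treatment in one arm, while in the other they include two weeks after treatment has ended. A reaction that reaches its worst grade after the last mark has a different chance of being graded when it occurs, depending on the arm. The trial is open-label, and these grades feed a between-arm comparison and a safety look, so unequal opportunity for detection matters.

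For SAEs, a site reading {22} and Table 3 together cannot tell whether a serious radiation event at, say, month 24 triggers individual notification or only a form entry. Grade 3 or higher late radiation events are a secondary objective, so these are events that the trial wants to know about.

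**Working it through.** The plan gives no figure of its own to reproduce; the check compares the stated windows.

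**Assumptions.** One month = 30.44 days. Radiotherapy ends on day 7 in the 1-week arm and day 21 in the 3-week arm, with no sequential boost. Weeks 1–3 end on day 21.

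**Acute row against the 90-day definition.** Post-treatment days covered = 21 − day on which radiotherapy ends.

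| Arm | RT ends | Post-RT days covered | Of 90 | Uncovered |
|---|---|---|---|---|
| 3-week | day 21 | 21 − 21 = 0 | 0% | 90 days (100%) |
| 1-week | day 7 | 21 − 7 = 14 | 16% | 76 days (84%) |

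Counted from the start of treatment, the row gives each arm the same 21 days. The imbalance lies in the post-treatment part, and that is the part to which the definition ties its end.

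**Sequential boost.** The note under Table 3 moves the post-radiotherapy assessment to week 2 or week 4, but does not say whether the acute row moves too. If it does not, and treatment ends on day 14 or day 28, the row covers 21 − 14 = 7 post-treatment days in the 1-week arm. In the 3-week arm it stops 28 − 21 = 7 days before treatment ends.

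**Next opportunity.** The month-3 visit falls at 3 × 30.44 = 91.3 days after radiotherapy, at or just past the 90-day boundary. An event first noted there could be classed as acute or late unless its onset is dated.

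**SAE windows.**
- First follow-up mark: about day 91, later than day 30. No follow-up SAE mark in Table 3 lies inside the 30-day window.
- Last mark: 60 × 30.44 = 1,826.4 days. 30 / 1,826.4 = 1.6% of the follow-up span.
- Late toxicity begins after day 90, so the 30-day limit expires 90 − 30 = 60 days before the late period opens.

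**The case against.** **On acute toxicity.** The 90-day rule classifies events by timing and is not a visit schedule. Table 3 gives both arms the same three weekly assessments on the same clock from the start of treatment. The text under the table records radiotherapy-related events at every visit, so month 3 can pick up earlier reactions by history. The first interim look is powered on a within-group rate against a 5% target, not on a contrast between arms. All of this is correct, and it means that the gap is between definition and schedule rather than a flat contradiction. It does not ensure that the worst grade over the window is obtained in the same way in both arms, and {20a} does compare arms.

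A reader might go further and infer one toxicity review in the test arm against three in the control arm, from the statement that "They will be reviewed weekly during treatment to discuss and manage any treatment-related adverse events". That section concerns adherence and patient management, not endpoint collection, and does not support the inference.

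**On SAEs.** The 30-day sentence follows the notification sentences and can be read as the end of individual notification, with Table 3 showing recording. That reading is plausible, but the article does not state it: {22} uses both recording and reporting and attaches one time limit.

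A reader might also infer that serious late events would never reach the monitoring committee. The documents do not support this. SAEs are recorded without a time limit, Data management {19} gives the committee access to data while the trial is ongoing, and {21a} gives it patient safety and sends its reports to the review boards. Nor do the biologically effective doses in Table 5 bear on a reporting window.

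**Conclusion.** The point holds as two limited inconsistencies.

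1. Followed as written, the acute row captures about 0 post-treatment days in the 3-week arm and about 14 in the 1-week arm, out of a defined 90. The only later opportunity inside or near the window is a visit at about day 91. The figures assume no sequential boost and treatment delivered on schedule. The article gives no onset-time distribution for acute reactions, so neither the size nor the direction of any resulting bias can be calculated. The documents support unequal opportunity for capture, not a demonstrated bias.

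2. The 30-day SAE sentence and the month-60 SAE marks are not reconciled. What is unclear is the duty to notify late radiotherapy-related SAEs individually to the review board and sponsor. The data themselves are not lost.

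Neither limb touches the primary endpoint, power or sample size. By the date in Trial status, 420 patients had been randomised, so the 50-per-arm accrual point had probably passed. A change would mainly protect the remaining 2,100 − 420 = 1,680 patients, later month-3 visits and the final adverse event comparison.

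**What to change.** **Acute toxicity.** Extend the acute row of Table 3 in both arms by recording, at the existing 3-month visit, the worst CTCAE acute grade since the start of radiotherapy with its onset date. Classify events as acute or late by onset date, not by the visit at which they were noted, and compare the arms on the window given in Secondary outcomes. State whether the acute row moves when a sequential boost is given. The cost is one added form field and some recall error, since reactions will be graded in retrospect at about three months.

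**SAEs.** Reconcile {22} with Table 3 by stating which window governs notification to the review board and sponsor and which governs recording in the database, so that late radiotherapy-related SAEs have a defined notification route. The choice of windows is for the sponsor. The cost is amendment wording and, depending on that choice, some additional reports from sites.
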